### Sample size

We will calculate the average number of providers who will be included from each of the 60 facilities (or 30 facilities in each arm) using a test of two proportions for a binary indicator of a present competency score. Competency will be assumed at a score of 80% or higher score on both the knowledge and skills assessments. We assumed that the proportion of competent providers will be 50% in the control group. The goal is to have at least 80% power to reject a null hypothesis that the proportions are equal across the two arms against the alternative hypothesis of a minimum effect size of 20 percentage point difference in proportions of competent providers. The test of hypothesis will be performed at 0.05 level of significance. Sample size was calculated using PASS statistical software [14]. Since some facility-level factors that are shared by the providers working in the same facility can influence the competency level, we will assume 0.05 within facility correlation of competency levels across providers in a given health facility**.** Assuming that an average of four (04) service providers sampled per health facility, a total of 240 providers across the two groups will be needed so that there will be at least 80% power to detect a 20 percentage point difference in competence level between the two arms (assessment at 3 months) at 0.05 level of statistical significance. The final sample size will be 300 or 150 providers per study arm to account for potential 20% drop-out at the time of post-training assessment. The participants for each facility will include the maternity unit head wherever possible and two others; to ensure the other team members receive the necessary support they need to practice the competencies. Study participants will be administered a single survey comprised of modules on characteristics, knowledge, and costs incurred in addition to a competency assessment prior to training and at three time points following training (end of training day, 3, 12 months post-training).

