### Randomization

The unit of randomization will be the health facility. All 60 facilities will be divided into 9 strata by 3 geopolitical zones and by level of healthcare delivery; each stratum is randomized to either control or intervention using randomly permuted blocks in ratio of 1:1 to achieve balance in type of facility and location by treatment arm. Health facilities will be matched prior to randomization and will be grouped as either receiving simulation-based LDHF/m-Mentoring or traditional training. As skilled birth attendants are few in the health facilities, all health providers working in maternity or newborn units who meet the inclusion criteria will be selected from the randomized health care facilities. Arm 1 will include birth attendants who will be trained using LDHF approach while arm 2 will be those who will be trained using TRAD approach.

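### The unit-head-plus-two sentence reads as three providers per facility (180 in all), which conflicts with the 240 assessed and 300 enrolled; followed literally, it misses the stated 80% power after the planned drop-out

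*Protocol article*

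**What the plan says.** All references are to the protocol article.

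- **Sample size, the calculation.** Power rests on "an average of four (04) service providers sampled per health facility" across 60 facilities, 30 per arm, which gives 240 in total for the 3-month comparison.
- **Sample size, the inflation.** "The final sample size will be 300 or 150 providers per study arm", to allow for 20% drop-out. Spread over 60 facilities, this implies an average of five enrolled per facility, although the article does not state that figure. The Abstract repeats 150 trainees per arm.
- **Sample size, the next sentence.** "The participants for each facility will include the maternity unit head wherever possible and two others". The reason given is that the rest of the team should be supported in practising the competencies.
- **Randomization.** Because skilled attendants are few, "all health providers working in maternity or newborn units who meet the inclusion criteria will be selected" from the randomized facilities.
- **Training approach 1 (LDHF arm).** The whole available team is trained, and those meeting the inclusion criteria are assessed. The section on the control arm gives no number per facility.

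**The concern.** Within one section, a sentence that reads as three providers per facility follows directly on a calculation that needs four assessed and, by implication, five enrolled. The same sentence departs from the all-eligible rule in Randomization. The article does not say which statement governs.

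The wording decides who enters the primary comparison at 3 months. A field team that treats the head and two others as the quota would enrol 180 rather than 300, a shortfall of 120/300 = 40%. The trial would then not have the power that the same section claims for its 20-point difference.

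**Working it through.** **Inputs (Sample size section unless noted)**
- 30 facilities per arm; 1:1 allocation (Randomization).
- The method: "using a test of two proportions for a binary indicator of a present competency score".
- Control proportion 0.50: "We assumed that the proportion of competent providers will be 50% in the control group".
- Effect 0.20, taken as 0.50 versus 0.70: "minimum effect size of 20 percentage point difference in proportions of competent providers".
- Intra-facility correlation 0.05; significance level 0.05; power goal at least 80%; drop-out 20%.
- Sidedness is not stated. Two-sided is assumed, and one-sided is shown alongside.

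**Formulas.** With m assessed per facility:
- Design effect DE = 1 + (m − 1) × 0.05
- Effective number per arm n = 30m / DE
- Power (pooled null variance) = Φ{[0.20 − 1.96 √(2 × 0.6 × 0.4 / n)] / √[(0.25 + 0.21) / n]}
- Power (unpooled) = Φ{0.20 / √(0.46 / n) − 1.96}

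**Step 1: reproduce the plan.** Without clustering, 93 per arm are needed (103 with continuity correction). Multiplying by DE = 1.15 for m = 4 gives 93 × 1.15 = 107 per arm, or 103 × 1.15 = 119 with the correction. The plan's 30 × 4 = 120 per arm meets both. The inflation 240 / (1 − 0.20) = 300 is exact. The plan's own figures hold.

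**Step 2: the count under three per facility.** 60 × 3 = 180 enrolled, 90 per arm. After 20% loss, 180 × 0.8 = 144 assessed, 72 per arm, an average of 2.4 per facility.

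**Step 3: power at each count**

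| Assessed per facility | Per arm | DE | Effective n per arm | Two-sided, pooled / unpooled | Two-sided, continuity-corrected | One-sided 0.05, pooled |
|---|---|---|---|---|---|---|
| 4 (as planned, after loss) | 120 | 1.15 | 104.3 | 0.844 / 0.854 | 0.807 | 0.909 |
| 3 (no loss) | 90 | 1.10 | 81.8 | 0.747 / 0.760 | 0.692 | 0.838 |
| 2.4 (three enrolled, 20% loss) | 72 | 1.07 | 67.3 | 0.662 / 0.677 | 0.594 | 0.770 |

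Worked example for the last row, unpooled: √(0.46 / 67.3) = 0.0827; 0.20 / 0.0827 − 1.96 = 0.46; Φ(0.46) = 0.68.

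**Step 4: detectable difference.** With 72 per arm, the difference from 50% that is detectable at 80% power (two-sided) is 22.9 points unpooled and 23.3 points pooled, so about 23 points.

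**Step 5: sensitivity to the correlation.** With the correlation set to 0, two-sided pooled power at three per facility is 0.787 with no loss and 0.691 after loss. At 0.10 it is 0.709 and 0.634. The two-sided shortfall therefore does not depend on the choice of 0.05.

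**The case against.** The strongest reply is that the article already has a selection rule, and it is not this one. Randomization states the all-eligible rule with its reason, the LDHF section assesses those who meet the inclusion criteria, and the Abstract and the Sample size section both give 150 per arm. The average of four is a planning assumption, which a census of eligible staff can satisfy. The sentence says that participants will *include* the head and two others, not that they are limited to them, so it could describe a minimum composition.

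Much of this stands. It would be wrong to infer that the article sets three mutually incompatible rules, because the all-eligible rule and the average of four to five can coexist. Nor does the text establish the head-plus-two sentence as the operative instruction, or the selection as purposive: only the head is named, and how the two others are chosen is not stated.

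What does not stand is that the sentence is harmless. It gives a specific number, and its stated purpose refers to other team members, which suggests a subset of the team rather than a floor. If a minimum was meant, the text does not say so. It cannot describe who is trained in the LDHF arm, where the whole team is trained. If it was meant only for the off-site arm, participants would be selected differently in the two arms, which would need correcting too.

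**Conclusion.** The point holds as an inconsistency in one sentence. On its natural reading the sentence gives 180 providers, against 240 assessed, 300 enrolled and the all-eligible rule.

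The power loss is conditional on the sentence being followed as a fixed number. In that case the 80% goal is missed under every variant examined once the planned 20% drop-out applies: 66-68% two-sided (59% with continuity correction) and 77% one-sided. With no loss the result depends on sidedness: 75-76% two-sided, but about 84% one-sided.

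A reader might go further and infer that the sample size is miscalculated or that the trial as planned is underpowered. The article does not support that. Its calculation gives 81-85% power (two-sided) at 240 assessed, the 300 follows exactly, and under the all-eligible rule the planned average may well be reached.

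**What to change.** Replace the sentence with one selection rule for both arms that agrees with Randomization and with the calculation. For example: all eligible providers in each facility are enrolled, including the maternity unit head wherever possible, with an expected average of five enrolled and four assessed per facility after 20% loss. No sample-size figure, procedure or analysis changes.

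If three per facility is really intended, restate the section instead: 180 enrolled, about 144 assessed, about 67% power for a 20-point difference, and 80% power for about 23 points (two-sided). The Abstract's 150 per arm and the all-eligible statement in Randomization would then need to change as well.

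In either case, state whether the 0.05 level is one- or two-sided. The cost is one sentence of wording or, on the second route, a less favourable stated power.

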### Training approach 1 and data collection: Simulation-based LDHF/m-mentoring training of participants - group 1 or intervention group

The training for the LDHF arm will be for the entire team of service providers available at the health facility, but only those who will meet the study inclusion criteria will be assessed. After oral consent is obtained, the participants will take pre-training assessments consisting of MCQs and OSCEs through use of manikins, to assess their baseline knowledge and skills. The MCQ contains a set of multiple choice questions to test trainees’ knowledge. OSCE involves the use of validated checklists to evaluate trainees’ demonstration of clinical skills to ensure that each step is correctly and completely carried out. The assessments will test their knowledge and skills on conduct of normal delivery, active management of the third stage of labor (AMTSL), neonatal resuscitation, case management of pre-eclampsia and eclampsia (PEE) and management of PPH (e.g. manual removal of placenta, internal bimanual uterine compression and compression of the abdominal aorta). The training will be divided into two “low-dose” training courses of 4 days each, with additional time for assessment as needed and will be conducted at the health facilities using the adapted basic emergency obstetrics and newborn care (BEmONC) package repeated after 1 month. The training techniques will be modified to shift the emphasis to practice. The time spent on lectures will be reduced and time spent on hands-on practice will be increased. The Peer Practice Coordinators (PPCs) will receive technical update in LDHF including the use of session plans, case scenario and MamaNatalie/NeoNatalie models to conduct simulation practices. At the end of the four-day training, the participants will undergo an immediate post-training assessment which includes MCQs and OSCEs. The questions answered correctly and procedure done competently is scored over a total of 100%. A test score of ≥80% is accepted as level of competence. The pre-training and immediate post-training assessments results will be compared. During the one-month intervals between training courses, health care providers will have the opportunity to practice what they learned and reinforce their competencies through high-frequency simulation-based practices of 2–3 times weekly. The PPCs will complete the practice log. In addition to the simulation exercises, all the trained providers in the LDHF arm will participate in mobile Mentoring (mMentoring), which consists of receiving weekly reminder messages and quiz questions on the topics reviewed via SMS messaging. Also the PPCs will receive structured, monthly half-hour mentoring calls from a trainer/master mentor that provide remote support, answering questions, providing guidance and reinforcing key messages. Skills and knowledge assessments will be done at three time points post-training (immediate post training day, at 3 months 12 months). Trainees’ satisfaction with the simulation-based LDHF/m-Mentoring training approach will also be determined using satisfaction (quantitative) survey.

Qualitative data will be collected through six (6) focus group discussions (FGD) comprising 8–10 similar participants per group purposively selected from among the trainees at 12 months based on their availability and experience. The FGD focuses on the experiences and satisfaction of trainees with LDHF training approach, and high-frequency practice sessions with simulators, mobile mentoring sms and quizzes, opinions about changes in clinical practice and outcomes and overall impressions of the LDHF approach and what could be improved. The FGD will last 60–90 min. In-depth interviews (IDIs) will also be conducted with PPCs and trainers at 12 months post-training by study staff. The IDIs for PPCs will aim at hearing their insights and experience managing simulator practice sessions for their facility, interacting and working with the trainers/master mentors, m-Mentoring, changes in clinical practice and outcomes, success and challenges and overall impression about LDHF approach. For the trainers, their thoughts and experience with the LDHF training approach, successes and challenges with mobile mentoring and supporting peer practice coordinators, opinions on the effectiveness of m-Mentoring, confidence in their role as trainers, successes and challenges in collecting data will be sought. Each IDI will last about 45 min and is audio recorded.

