**Methods:**

This will be a prospective cluster randomized control trial. Sixty health facilities will be randomly assigned for *day of birth care* health providers training through either LDHF plus mobile mentoring (intervention arm) or TRAD (control arm). There will be 150 trainees in each arm. Multiple choices questionnaires (MCQs), objective structured clinical examinations (OSCEs), cost and satisfaction surveys will be administered before and after the trainings. Quantitative data collection will be done at months 0 (baseline), 3 and 12. Qualitative data will also be collected at 12-month from the LDHF arm only. Descriptive and inferential statistics will be used as appropriate. Composite scores will be computed for selected variables to determine areas where service providers have good skills as against areas where their skills are poor and to compare skills and knowledge outcomes between the two groups at 0.05 level of statistical significance.

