### Training approach 2 and data collection: Traditional group training of participants – Group 2 or control group

The traditional training approach will consist of 8 days of lectures with practice sessions on simulators, off-site the participants’ workplace, usually in a hotel. Oral consent will be obtained, the participants will take pre-training assessments consisting of MCQs and OSCEs through use of manikins, to assess their baseline knowledge and skills respectively. The assessments will test their knowledge and skills on conduct of normal delivery, AMTSL, neonatal resuscitation, case management of PEE and management of PPH (e.g. manual removal of placenta, internal bimanual uterine compression and compression of the abdominal aorta). This group then receives lectures and practice sessions on conduct of normal delivery, AMTSL, neonatal resuscitation, case management of PEE and management of PPH. The Nigerian BEMONC package and clinical observation checklists are used during the training sessions. The group-based training approach will include training sessions consisting of 8 days of lectures and fewer practice sessions using manikins (MamaNatalie/NeoNatalie) offsite and not at the trainees’ place of work. Table 1 outlines the basic similarities and difference between the two groups. At the end of the eight-day training, the participants will undergo an immediate post-training assessment which includes MCQs and OSCEs. As described among arm 1, the questions answered correctly and procedure done competently will be scored out of a total of 100%, assessments results will be compared and trainees satisfaction survey will be conducted.

**Table 1 Tab1:** Comparison of the Simulation-based LDHF and Group-based study arms

Parameters of the interventions received	Simulation-based LDHF Arm	Group-based Arm
Training covers BEMONC	Yes	Yes
Training is onsite	Yes	No
More frequent practise sessions using manikins during training	Yes	No
Post-training Practise Sessions with manikin in facility	Yes	No
Presence of PPCs	Yes	No
Use of mobile phone for post-training support	Yes	No
All courses divided into two phases which are 1 month apart	Yes	No

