### Data analysis

#### Primary outcome

Clinical competency level in BEmONC skills of service providers at 3 months post-training.

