#### Inferential analysis

Generalized linear model with robust facility-level variance will be used to test the differences between arms in MCQ scores, OSCE scores and satisfaction outcomes at 3 months using a group indicator as the main predictor in the model. Additionally, we will adjust for provider- and facility-level characteristics that show imbalance between arms at baseline and can be strongly correlated with the outcome scores. A *p*-value < 0.05 will be considered statistically significant. The number of short messages sent is assessed for trend of the reply and correct answers. The frequency and trend of mentorship call will also be assessed. The model described for the primary outcome is used to look at the outcomes at other time points. In addition, we will develop a longitudinal model that assess the change in scores (or competency level) over time post-training. This model is appropriate, since it accounts for correlation within a provider over time as well as within-facility correlation of scores. Generalized linear population-average model estimated using generalized estimating equations (GEE) with working exchangeable correlation structure is used. The amount of missing data is assessed for each variable and overall for the sample. If more than 5% of data are missing, multiple imputation procedure is used assuming missing at random. Composite scores is computed for the satisfaction survey. A Decision Tree will be used to compare incremental costs and incremental effects by provider across the two study arms. One-way, multi-way and probabilistic sensitivity analyses are conducted to assess uncertainty.

Qualitative data analysis: Notes and transcripts will be entered into Atlas-ti version 8 software. Content analysis of the discussions will be undertaken to generate themes of interest along which the analysis will be done. Analysis will be by themes across location and classifications of the groups.

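### The 'immediate post-training' test appears to follow 4 of 8 course days in the LDHF arm but all 8 in the traditional arm, so between-arm and over-time analyses that use it are not like for like

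*Protocol article*

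**What the plan says.** Two sections of the protocol article describe the training, and each places a test with the same name.

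- **LDHF (Training approach 1).** There are two four-day courses. Table 1 confirms the split, answering yes for LDHF and no for the group-based arm to: "All courses divided into two phases which are 1 month apart". On testing, the section says: "At the end of the four-day training, the participants will undergo an immediate post-training assessment which includes MCQs and OSCEs". Two sentences on scoring and one on the pre/post comparison follow. The text then moves on: "During the one-month intervals between training courses, health care providers will have the opportunity to practice what they learned and reinforce their competencies".
- **Traditional arm (Training approach 2).** There is one course: "At the end of the eight-day training, the participants will undergo an immediate post-training assessment which includes MCQs and OSCEs".

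The Sample size section gives both arms one schedule: "prior to training and at three time points following training (end of training day, 3, 12 months post-training". The Study design section does the same.

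The Descriptive analysis section calculates the percentage competent in each group before training and at the later assessments. The Inferential analysis section first sets out the between-arm model at 3 months and then adds: "The model described for the primary outcome is used to look at the outcomes at other time points". It also plans a GEE model for change in scores or competency over the post-training period.

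The primary outcome is "Clinical competency level in BEmONC skills of service providers at 3 months post-training". The listed learning outcome among the secondary outcomes is retention at 12 months. The immediate test is in neither list.

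**The concern.** In the traditional arm, the end of training is one date. In the LDHF arm it can be either of two dates about a month apart, and the wording points to the earlier one. If so, a shared label covers two different states: a fully taught control arm, and an intervention arm with its second course still to come.

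Two planned analyses would then be hard to read. The immediate between-arm contrast would not compare the two completed programmes. In the longitudinal model, the LDHF change after the immediate test would contain a further four-day course while the traditional arm's contains none. A difference in slope could then be mistaken for better retention, which is the claim such a trial most wants to make.

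**Working it through.** The plan gives no figure on this point, so there is none to reproduce. The check is a count of days followed by a short piece of algebra.

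**Inputs from the article:** LDHF 2 × 4 = 8 course days, courses one month apart; traditional arm 8 course days in one block.

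**Assumptions:** training starts on day 1 and a month is 30 days. The traditional course ends on day 8 and LDHF course 1 on day 4. LDHF course 2 ends on day 31 + 3 = 34 if the month runs from start to start, or on day 4 + 30 + 4 = 38 if it runs from the end of course 1 to the start of course 2.

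**Course days around the immediate test**

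| When LDHF is tested | LDHF day | LDHF days taught | Traditional days taught | LDHF days still to come | Traditional days still to come |
|---|---|---|---|---|---|
| After course 1 (natural reading) | 4 | 4/8 = 50% | 8/8 | 8 − 4 = 4 | 8 − 8 = 0 |
| After course 2 | 34 to 38 | 8/8 | 8/8 | 0 | 0 |
| After each course | 4, and 34 to 38 | as above | 8/8 | as above | 0 |

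In the third row, the article does not say which LDHF test would enter the between-arm analysis.

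**What the first row does to the estimates.** Let F be the LDHF mean score at the end of course 2, and G the change between the end of course 1 and the end of course 2. Let T be the traditional mean on day 8, and D_L and D_T the losses from the end of full training to the 3-month visit.

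- Immediate contrast: (F − G) − T = (F − T) − G.
- Change to 3 months: LDHF is (F − D_L) − (F − G) = G − D_L; traditional is −D_T. The difference in change is (D_T − D_L) + G.
- Contrast at 3 months: (F − D_L) − (T − D_T). G does not appear.

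The same unknown G enters the immediate contrast with a minus sign and the difference in change with a plus sign. If G is positive, the first understates the completed LDHF programme and the second overstates its retention. The documents give no learning or decay rate, so neither the size nor the sign of G can be fixed. The 3-month contrast does not depend on where the immediate test is placed.

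The sample size is untouched: 60 facilities × 4 providers = 240, and 240 / (1 − 0.20) = 300, both tied to the 3-month assessment.

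**The case against.** Several objections have force.

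- **Course 1 is inferred from sentence order.** The LDHF section is not strictly chronological, and it allows extra assessment time for the courses generally. A test after course 2, or after each course, is possible. This stands, which is why the point is put as the natural reading and not as a certainty.
- **The test carries limited weight.** It is not a listed outcome, its one explicit use in the LDHF section is a within-arm comparison with the pre-test, and the 12-month outcome alone could satisfy the phrase about other time points. The weight is indeed limited. Even so, the Sample size and Study design sections list the test as a post-training time point for both arms, and the Data analysis section summarises and models such time points by arm.
- **Spaced learning is the intervention.** Practice, text messages and calls continue in LDHF whatever the starting point, so no choice of test date makes the slope a measure of passive retention. This is correct. Moving the test removes only the extra taught course from the trend.

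A reader might infer two stronger things, and the documents support neither.

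1. *LDHF has had only half the content when tested.* The LDHF section says the package is repeated after a month, so half the days need not be half the content.
2. *LDHF is examined sooner after its last course at the primary visit.* With 3 months as 91 days, counting from the end of course 1 would give 95 − 38 = 57 to 95 − 34 = 61 days since the last LDHF course, against 91 in the traditional arm. Counting from baseline would give 53 to 57 against 83. But the article treats the training as one whole divided into two courses, so '3 months post-training' most naturally means after both, giving 91 against 91. The Abstract's "Quantitative data collection will be done at months 0 (baseline), 3 and 12" reads as shorthand, since it also leaves out the immediate test. The exact anchor may also sit in the full protocol, which is not shown.

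**Conclusion.** The concern holds for the immediate test and for what is built on it. On the natural reading, the between-arm comparison at that test is 4 of 8 course days against 8 of 8, and the later trend contains 4 further course days in LDHF and 0 in the traditional arm. A slope difference from that model could not be read as a retention difference.

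This rests on two readings: that the LDHF test follows course 1, and that the immediate test enters the by-arm summaries and models. Both are the more natural reading; neither is beyond doubt. No bias in scores is quantified, and no gap or bias is shown at the 3-month primary assessment. It is a specific correction to a secondary part of the analysis, and confidence in it is moderate.

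**What to change.** In both training sections and in the Inferential analysis section, define the immediate post-training test used for between-arm and longitudinal analyses as the one at the end of the full training: the end of course 2 in LDHF and day 8 in the traditional arm. If a test after LDHF course 1 is kept, call it interim and use it only within that arm.

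**Cost.** No participants are added, and simply moving the test adds no assessment round. Keeping a course-1 test as well adds one MCQ/OSCE round for up to 150 LDHF providers and an extra test exposure in that arm only. The LDHF immediate test moves from day 4 to day 34 to 38, about a month later, and then follows a month of practice and mentoring. That is part of the LDHF strategy, but it should be noted when slopes are interpreted.

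**Minor note.** State that the 3- and 12-month assessments run from the end of the full training, or name another anchor, and report days since last course by arm. With the first anchor, and 12 months as 365 days, the last LDHF visit falls on day 34 + 365 = 399 to 38 + 365 = 403, against 8 + 365 = 373 in the traditional arm. The 12-month availability criterion and the one-year cost horizon should then be worded to match.
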